##### Multidimensional Craving Measurement and Sense of Presence in VR

During VR therapy, craving and the sense of presence in VR training will be measured. Craving will be detected through both subjective and objective measures: a visual analog scale (VAS) to evaluate the perceived craving intensity on a scale from 0 to 10, based on the specific moment in which it will be administered. Furthermore, craving will be objectively evaluated with biofeedback EvU-TPS through the detection of the following psychophysiological measures: heart rate, heart rate variability, skin conductance, and skin temperature. The sense of presence will be measured through the ITC-SOPI self-report at the end of the virtual session. The Addiction Medicine Unit in collaboration with NEUROFARBA is working on a study to assess the psychometric properties of ITC-SOPI in its Italian version.

#### Training Course for Treatment Providers

After the development of the VR environments and the definition of the measures and procedures involved in the study, the next step consisted in training the treatment providers involved (psychologists and psychotherapists) and in a verification of learning after the training course. This represented a very important point as one of the factors that affect the efficacy of interventions in the health domain is the good quality of the training administered to the people who implement the programs (69). Indeed, training allows those who carry out the intervention to become confident with it (70). Moreover, some interventions need certain competencies that can be acquired only with specific training courses (71). In particular, a well-planned training course provides basic theoretical knowledge, clear program goals and objectives, modeling, and practice of effective intervention strategies, regular coaching, and constructive feedback (72). The training course consisted in 2 lessons on biofeedback, 2 lessons on CBT and diaphragmatic breathing, 1 lesson on VR theory, hardware and software application, and hygiene rules for virtual instruments. All lessons lasted 3 h, for a total duration of 15 h of training. Due to COVID-19 restrictions, the lessons were organized in a mixed modality, online and offline simultaneously. Two *ad hoc* questionnaires were created to assess the following variables: the first questionnaire had 13 questions and assessed electrodermal activity, skin conductance, photoplethysmography, heart rate, heart rate variability, the psychophysiological state of relaxation of the participants, their respiratory rate, and biofeedback training. The second questionnaire had ten questions and assessed respiratory training, mastery strategy, disputing, systematic desensitization, VR therapy, and cybersickness.

To analyze the efficacy of the training course for the psychotherapists involved in *Alter Game*, we proceeded to a pre-post design with a follow-up in which the above-listed variables were measured before the beginning of the training course (pre-test), after the last meeting of the training course (post-test), and 1 month after the conclusion of the course (follow-up). The treatment providers were provided with training material in the form of slides and guides to facilitate study and consultation in case of need. The coordinating psychologist sent the questionnaires *via* e-mail the day before the lessons for the pre-test, and then again after the end of each of the expected 2 training cycles. The first cycle included the 2 biofeedback lessons and, the second, the 3 lessons about CBT, diaphragmatic breathing, and VR. All training sessions were organized on the Meet platform, ensuring the mixed modality and the possibility to follow lessons in a deferred mode since everything was videotaped and made available to all the trainees on a shared drive folder. Training was provided by Righetto S.r.l. (as far as electromedical equipment was concerned) and by Plumake S.r.l. (for what concerned the hardware and virtual software dimension), respectively. The meetings concerning the training in psychotherapy techniques and VR therapy were organized by psychologist-psychotherapist collaborators.

#### Efficacy Evaluation of the Integrated Intervention

##### Design

We will conduct a pre-test/post-test experimental design with a 1-month follow-up.

Two independent groups to which patients will be randomly assigned will be considered. One group will undergo a traditional CBT treatment of 16 sessions (the CBT group), while the second group will undergo the integrated treatment, consisting of 8 CBT sessions and 8 sessions of psychotherapy based on VR cue-exposure therapy, each with a different environment (the CBT + VR group). Each session will last 1 h. To better control the effects of the training in VR on pathological gamblers, the psychophysiological parameters of craving will be measured through biofeedback and VAS at each session of the training (multi-method measurement of craving).

To verify the efficacy of the intervention, one measurement session is planned before the beginning of the treatment (pre-test), and one at the end of the treatment (post-test). For the assessment of the maintenance of any changes at post-test, an additional measurement is planned 1 month after the end of the treatment (follow-up). The three measurement sessions are planned for both the CBT group and the CBT + VR group. In each measurement session, perceived self-efficacy in managing gambling behavior, craving, gambling-related cognitive distortions, impulsivity, personality traits, and pathological gambling symptoms will be measured in both groups.

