### Recruitment

We will recruit a sample of about 60 patients with GD who are referred to the Addiction Medicine Unit of Verona (G. B. Rossi Hospital). This sample size is consistent with the power analysis we conducted *a priori*. Using G^*^Power software to estimate the sample size that would be necessary to achieve a statistical power of 0.95 for a mixed ANOVA, indeed, revealed that a sample size of *n* = 58 was necessary in order to obtain an average effect size, equal to 0.40 (α = 0.05).

Inclusion criteria will be: (a) being male and female subjects over 18 years of age and under 65 years of age; (b) being addicted to slot machines, scratch cards, lotto, SuperEnalotto (because environments were created with these specific cues); (c) informed consent signature. An inclusion criterion (b) will be evaluated by a clinical interview based on the DSM-5 diagnostic criteria in the first psychological assessment session and by SOGS, which reports the type of gambling games played by gamblers.

Exclusion criteria will be the presence of: (a) antisocial personality traits; (b) borderline personality traits; (c) high levels of impulsivity; (d) thought disorders; (e) delusional disorders. Exclusion criteria (a), (b), and (c) were chosen to identify the presence of gamblers probably categorized as “third pathway” to Blaszczynski and Nower (55) and that, therefore, may be more exposed to risks of relapse following immersive VR exposure to environments with trigger cues. Excluding these patients will allow us to guarantee greater safety for them by administering treatment as usual.

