Patients meeting the inclusion criteria will be randomly assigned to the CBT group or to the CBT + VR group. The CBT group will follow a full cycle of psychotherapy that will consist of 16 weekly sessions, lasting 60 min and will make use of techniques belonging to an evidence-based cognitive-behavioral approach. For the CBT + VR group, there will be a first cycle of traditional psychotherapy that will consist of 8 weekly sessions, each lasting 60 min, which will also make use of evidence-based cognitive-behavioral approach techniques. Following this, psychotherapy based on virtual exposure will be carried out, which will again comprise 8 weekly sessions, marked by: systematic desensitization therapy in virtual reality exposure therapy, cognitive restructuring, and emotional management/literacy. Each virtual session will last 60 min, 20 min of which will be dedicated to virtual exposure. About 20 mins is the recommended limit of the duration of immersions in virtual reality because eyestrain and headache may occur for longer exposures (76, 77). We adopted this safety limit at least until empirical data document the safety of VR immersion with gamblers (10). An extinction process needs more time to originate, but limiting the duration of the immersion is necessary due to ethical considerations (10).

The virtual session will be structured as follows. In the first session, the virtual protocol will be presented to the patient, and virtual training will be carried out to provide the skills related to the use of the instrumentation (Figure 11). Biofeedback parameters will also be measured 5 min before the session. From the second to the eighth sessions, the biofeedback parameters will be measured 5 min before the beginning of the session (in the study, the baseline rate), and the measurements will be resumed during the entire exposure to the virtual environment. The patient will be asked about the intensity of the craving felt during both measurements and at the end of each session *via* VAS. As mentioned above, the technique used in conjunction with virtual cue exposure therapy will be systematic desensitization, which is a psychotherapeutic CBT treatment consisting in alternating phases of exposure to the trigger cues to phases of bodily relaxation, with the aim of reinforcing the relaxation response even in the presence of specific reactive cues (78, 79).

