## Data Analysis

In general, all the patients' demographic and clinical characteristics will be summarized using descriptive statistical methods. In particular, mean, median, and standard deviations will be used for symmetrically distributed continuous variables, median and interquartile distance for asymmetrically distributed continuous variables, and frequency distributions for categorical variables. Multi-method analysis of craving measurement in order to draw up a physiological and psychometric profile of craving (using biofeedback) will be performed. This analysis will be conducted through linear correlation measures. For the analysis of the efficacy of the training course for the treatment providers, Student's *t*-tests for dependent samples or Wilcoxon's non-parametric test for paired samples will be used. Contingency tables and McNemar tests may also be used. For the analysis of the efficacy of the CBT + VR group compared to the CBT group, a mixed ANOVA will be performed for repeated measures with *Time* as within factor (pre-test/post-test/follow-up) and *Group* as between factor (the CBT + VR group/the CBT group).

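### The 1-month follow-up is meant to show maintenance, but no omnibus effect of the three-occasion mixed ANOVA, the only efficacy analysis named, answers that question

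*Protocol article*

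**What the plan says.** Under Design, the article plans a pre-test, a post-test and one later measurement, and states why the last is there: "For the assessment of the maintenance of any changes at post-test, an additional measurement is planned 1 month after the end of the treatment". It applies to both arms: "The three measurement sessions are planned for both the CBT group and the CBT + VR group".

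Under Data Analysis, the comparison of the arms is one sentence: "a mixed ANOVA will be performed for repeated measures with *Time* as within factor (pre-test/post-test/follow-up) and *Group* as between factor". No term of the model is singled out as deciding efficacy, and no contrast involving follow-up is named. The remaining analyses in that section concern the correlation of craving measures, the training of treatment providers, attrition and session attendance. None of them addresses maintenance.

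Under Recruitment, the sample size was chosen "to achieve a statistical power of 0.95 for a mixed ANOVA", giving n = 58 for an effect size of 0.40 at α = 0.05. The Discussion ties the directional hypothesis to the end of the psychotherapy sessions.

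**The concern.** The article sets a question for the follow-up and names an analysis that does not decide it. The Group x Time interaction asks whether the between-arm difference is constant over the three occasions. It is not constant if an advantage appears and stays, and it is not constant if an advantage appears and vanishes. A significant result fits both.

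This matters because relapse prevention is the rationale of the trial. After the post-test result, whether the advantage is still present a month later is the next thing a reader will want to know. If the plan is followed exactly as written, it yields no valid inference on that point.

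**Working it through.** **Inputs.** From the article: two randomised groups, three occasions, about 60 patients, expected retention of at least 80%, α = 0.05. Assumed, because the article does not give them: 1:1 allocation, hence 0.80 × 60 / 2 = 24 per arm; a post-test advantage d of 0.5 or 0.8 SD; correlation r between occasions of 0.5 or 0.7.

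**The plan's own figure.** Take 0.40 as Cohen's f, with m = 3 and r = 0.5. For the Group main effect, λ = f²·N·m / (1 + (m − 1)r) = 0.16 × 58 × 3 / 2 = 13.92 on 1 and 56 df, power 0.956. N = 58 is therefore reproduced. The interaction with the same inputs, λ = f²·N·m / (1 − r), needs only N = 18. Among the other interaction conventions tried, none gave 58 (closest 52).

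**Interaction, equal correlations.** With n per arm, λ = (n/2) × SS / (1 − r) on 2 and 2(2n − 2) df. SS is the sum of squared deviations of the between-arm differences from their mean over the occasions.

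- Kept (0, d, d): mean 2d/3, SS = (4/9 + 1/9 + 1/9)d² = 2d²/3.
- Lost (0, d, 0): mean d/3, SS = (1/9 + 4/9 + 1/9)d² = 2d²/3.
- Half kept (0, d, d/2): mean d/2, SS = (1/4 + 1/4 + 0)d² = d²/2.

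For n = 24, d = 0.8, r = 0.5, kept and lost both give λ = 12 × 0.4267 / 0.5 = 10.24. Half kept gives 12 × 0.32 / 0.5 = 7.68.

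**Group main effect.** λ = (n/2) × 3 × (mean difference)² / (1 + 2r). For d = 0.8, r = 0.5: kept 36 × 0.2844 / 2 = 5.12; lost 36 × 0.0711 / 2 = 1.28.

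Power with 24 per arm:

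| r | d | Interaction, kept | Interaction, lost | Interaction, half kept | Group, kept | Group, lost |
|---|---|---|---|---|---|---|
| 0.5 | 0.5 | 0.404 | 0.404 | 0.312 | 0.283 | 0.106 |
| 0.5 | 0.8 | 0.812 | 0.812 | 0.683 | 0.601 | 0.198 |
| 0.7 | 0.5 | 0.617 | 0.617 | 0.490 | 0.244 | 0.097 |
| 0.7 | 0.8 | 0.962 | 0.962 | 0.893 | 0.525 | 0.173 |

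**Interaction, unequal correlations.** Simulation with N = 60, 20,000 runs, uncorrected F, kept against lost:

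| Pre-post / pre-follow-up / post-follow-up | d = 0.5 | d = 0.8 |
|---|---|---|
| 0.5 / 0.5 / 0.8 | 0.550 vs 0.612 | 0.906 vs 0.978 |
| 0.7 / 0.49 / 0.7 | 0.604 vs 0.682 | 0.953 vs 0.989 |
| 0.5 / 0.4 / 0.7 | 0.492 vs 0.553 | 0.875 vs 0.951 |

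The Greenhouse-Geisser correction keeps the order (first row, d = 0.5: 0.513 vs 0.558).

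**A contrast that separates the cases.** The between-arm difference in pre-test-to-follow-up change (N = 60, r = 0.5) has power 0.48 (d = 0.5) or 0.86 (d = 0.8) if the advantage is kept, and 0.05 if it is lost.

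**Precision of the fix.** 95% half-widths with n = 24 per arm and t ≈ 2.01:

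- Follow-up difference adjusted for pre-test, t × √[(2/n)(1 − r²)]: 2.01 × 0.250 = 0.50 SD (r = 0.5); 2.01 × 0.206 = 0.41 SD (r = 0.7).
- Difference in post-test-to-follow-up change, t × √[(2/n) × 2(1 − r)]: 2.01 × 0.289 = 0.58 SD; 2.01 × 0.224 = 0.45 SD.

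**The case against.** The strongest reply is that this is a journal article. Contrasts within a named model are commonly left to the full protocol or analysis plan, the Data Analysis section does not exclude them, and keeping follow-up as a level of Time makes them available. That stands as far as it goes: the absence of a list of contrasts is no finding. What remains is that the article itself states the purpose and the analysis, and the two do not meet.

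Four stronger readings are tempting and are not supported.

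- A reader might infer that the interaction is the only planned test. A mixed ANOVA also gives main effects, and n = 58 reproduces as the Group main effect. That effect does respond to retention, but a lost advantage still triggers it about 20% of the time at d = 0.8, r = 0.5, four times α.
- A reader might infer that kept and lost advantages are always equally likely to be significant. That is exact only under sphericity. Sixteen weekly sessions separate pre-test from post-test and one month separates post-test from follow-up, so equal correlations are doubtful. In the unequal cases tried, the departure made the problem worse.
- A reader might infer that the investigators will read a significant interaction as maintenance. The article says nothing of the kind; the risk is that nothing in it prevents that reading.
- A reader might take a follow-up interval that excludes zero as proof of maintenance. It shows only a remaining advantage: a fall from 0.8 to an observed 0.55 SD would still exclude zero with a half-width of 0.50.

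It can also be said that maintenance of changes may be meant within each arm. The Time main effect does not rescue that reading: it pools the arms, and under the same model occasion means of (0, c, c) and (0, c, 0) again give the same sum of squares.

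**Conclusion.** The point holds in limited form: none of the omnibus effects of the named ANOVA answers the maintenance question that the article sets for its follow-up. Under sphericity the interaction's indifference between a kept and a lost advantage holds for any d and r. The sizes quoted (0.40 to 0.96 for both patterns with 24 per arm) depend on the assumed d, r, retention and 1:1 allocation. Losing half the advantage lowers interaction power only from 0.81 to 0.68 at d = 0.8, r = 0.5. The inference on efficacy at the end of therapy is not affected. The change is worth making before data are analysed, because it concerns a stated purpose of the trial and needs no new data.

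**What to change.** Add to Data Analysis, for each outcome:

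- The between-arm difference at post-test and at follow-up, each adjusted for the pre-test value, with 95% CI. The follow-up difference is tested only if the corresponding post-test difference is significant.
- The between-arm difference in post-test-to-follow-up change, with 95% CI.
- A rule of interpretation: a follow-up interval that excludes zero is described as an advantage still present at 1 month, and the change interval shows how much may have been lost. Neither a significant omnibus interaction nor a non-significant loss is read as maintenance.

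The fixed sequence controls α within one outcome only; the article lists self-efficacy, craving and cognitive distortions, so it does not settle multiplicity across them.

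The cost is wording. The downside is wide intervals, about ±0.41 to ±0.50 SD at follow-up and ±0.45 to ±0.58 SD for the change (24 per arm, r from 0.7 to 0.5), so fewer claims of maintenance can be made.

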### Recruitment

We will recruit a sample of about 60 patients with GD who are referred to the Addiction Medicine Unit of Verona (G. B. Rossi Hospital). This sample size is consistent with the power analysis we conducted *a priori*. Using G^*^Power software to estimate the sample size that would be necessary to achieve a statistical power of 0.95 for a mixed ANOVA, indeed, revealed that a sample size of *n* = 58 was necessary in order to obtain an average effect size, equal to 0.40 (α = 0.05).

Inclusion criteria will be: (a) being male and female subjects over 18 years of age and under 65 years of age; (b) being addicted to slot machines, scratch cards, lotto, SuperEnalotto (because environments were created with these specific cues); (c) informed consent signature. An inclusion criterion (b) will be evaluated by a clinical interview based on the DSM-5 diagnostic criteria in the first psychological assessment session and by SOGS, which reports the type of gambling games played by gamblers.

Exclusion criteria will be the presence of: (a) antisocial personality traits; (b) borderline personality traits; (c) high levels of impulsivity; (d) thought disorders; (e) delusional disorders. Exclusion criteria (a), (b), and (c) were chosen to identify the presence of gamblers probably categorized as “third pathway” to Blaszczynski and Nower (55) and that, therefore, may be more exposed to risks of relapse following immersive VR exposure to environments with trigger cues. Excluding these patients will allow us to guarantee greater safety for them by administering treatment as usual.

We also identified particularly vulnerable populations that may not be included in the study: (a) patients suffering from epilepsy because HMD can provoke epileptic seizures like other devices that produce visual effects (as described in the HTC-VIVE official user's guide); (b) visually impaired patients and hearing impaired patients because they would have limitations in the use of the virtual experience concerning sounds and visual aspects; (c) patients with cardiovascular problems because our psychophysiological measures of interest could be altered by these pathologies; (d) gamblers with vestibular problems because they may fall during the virtual reality experience due to vertigo, motion sickness, and imbalance (73); (e) patients with neurological disorders: e.g., individuals with migraine are more susceptible to visual discomfort (74); (f) patients with schizophrenia or psychotic traits because the available data on immersive VR in schizophrenic subjects are currently limited (75), and no data were available on gamblers with psychotic diseases and immersive VR treatment.

Patients with the onset of cybersickness for two consecutive virtual sessions will exit from the study *in itinere* and will be able to undertake a path of psychotherapy as usual in the Addiction Medicine Unit.

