Moreover, we will pay attention to the issue of an attrition rate. We are expecting to find a retention rate of at least 80% (78, 79) to avoid that participant loss will bias research outcomes. After that, we will check for any significant difference between the two treatment groups (CBT and CBT + VR) to verify if there is a differential attrition rate. In particular, we will compare the average number of meetings attended by the participants between the two treatment groups through *t*-tests, and we will compare the presence of drop-outs across the two groups through Chi-square tests. Moreover, we will determine if there are any significant differences (at the baseline) between participants who will complete the post-test session and those who will not in order to verify if specific subgroups of participants have a higher drop-out risk. This analysis will be conducted separately for each group. If any significant differences between participants of the two treatment groups will be found, we will verify that systematic attrition does not occur and we will conduct the analyses to verify the effects of the two interventions (CBT and CBT + VR) with the participants who completed the baseline and post-test assessments. Those lost to post tests will be excluded. If significant differences between participants of the two treatment groups will be found for the average number of meetings attended and the treatment drop-out, and participants who will complete the post-test session will be significantly different from those who will not, subsequent analyses will be conducted by using the last observation carried forward (LOCF) to assess the effects of attrition. Furthermore, we will examine within-group changes in outcomes as a function of session attendance to assess the effects of intervention non-compliance on outcomes. These subsequent analyses will be conducted, not excluding participants who will be lost to post-test and by imputing values for the follow-up variables for the participants who will not complete the post-test assessment.

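### The recruitment target of about 60 carries no attrition allowance: at the plan's own 80% retention floor, 48 patients are analysed against the 58 its power analysis requires

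*Protocol article*

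**What the plan says.** Under Recruitment, the protocol article states the target: "We will recruit a sample of about 60 patients with GD". It justifies this with a G*Power calculation for "a statistical power of 0.95 for a mixed ANOVA", which "revealed that a sample size of *n* = 58 was necessary" at an effect size of 0.40 and α = 0.05. It then concludes: "This sample size is consistent with the power analysis we conducted". The paragraph makes no allowance for drop-out.

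Under Data Analysis, the attrition paragraph says "We are expecting to find a retention rate of at least 80" per cent. For the comparison of the two interventions it uses participants who completed the baseline and post-test assessments: "Those lost to post tests will be excluded". Last observation carried forward is a follow-on analysis. It is triggered only if attendance and drop-out differ between the groups and completers also differ from non-completers.

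The Discussion describes drop-out among pathological gamblers as high and gives this as a reason for the short follow-up.

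**The concern.** A power calculation gives the number of patients who must be in the analysis. If the analysis drops patients without a post-test, the number recruited has to exceed that figure by the expected loss. Here the required number is 58 and the recruited number is about 60, yet the same article accepts a loss of up to one patient in five. The statements are in different sections and are not reconciled.

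The sample-size sentence is the article's only justification for the size of the trial. A reader of a null result would take from it a 5% chance of missing the assumed effect. If retention is near the accepted floor, that chance is larger than stated.

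**Working it through.** **Inputs from the protocol article**

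- Recruitment: about 60 patients; required n = 58; power 0.95; effect size 0.40; α = 0.05 (Recruitment).
- Two randomised groups (Design).
- Three occasions: pre-test, post-test and follow-up (Data Analysis).
- Retention of at least 80%; those lost to post-test excluded (Data Analysis).

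**Inputs assumed because the article does not state them**

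- The effect size is Cohen's f, the metric G*Power uses for ANOVA.
- The effect tested is the between-groups main effect.
- The correlation among repeated measures is ρ = 0.5, the G*Power default.
- Allocation is 1:1.

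**Step 1: headcount (none of the assumed inputs is needed)**

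- Margin: 60 − 58 = 2, and 2/60 = 3.3%.
- Analysed at the retention floor: 60 × 0.80 = 48.
- Shortfall: 58 − 48 = 10.

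**Step 2: reproduce the stated 58**

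For the between-groups test in a repeated-measures ANOVA with m occasions, the noncentrality is

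λ = f² × N × m / [1 + (m − 1)ρ], with 1 and N − 2 degrees of freedom.

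With f = 0.40, m = 3 and ρ = 0.5, λ = 0.16 × N × 3 / 2 = 0.24N.

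- N = 56: λ = 13.44, power 0.9495.
- N = 58: λ = 13.92, power 0.956.

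So 58 is the smallest even total that reaches 0.95, which matches the article. Other variants with f = 0.40 and m = 3 do not give 58:

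- Group × Time interaction in G*Power's default metric, ρ = 0.5: 18.
- The same interaction under other effect-size conventions: 52, 100 or 102.
- One-way ANOVA: 84.

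**Step 3: power at the numbers analysed**

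| Retention of 60 | Analysed | λ = 0.24N | Power |
|---|---|---|---|
| 100% | 60 | 14.40 | 0.962 |
| 95% | 57 | 13.68 | 0.953 |
| 90% | 54 | 12.96 | 0.942 |
| 80% | 48 | 11.52 | 0.913 |

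The chance of missing the assumed effect is 1 − 0.956 = 4.4% at 58 and 1 − 0.913 = 8.7% at 48.

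**Step 4: sensitivity to the assumed correlation**

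With everything else unchanged, power at 48 is 0.960 for ρ = 0.3 and 0.858 for ρ = 0.7. Those correlations would require totals of 46 and 68, so neither is consistent with the stated 58. They show how far the power figure depends on an input that the article does not give.

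**The case against.** **The 80% is a floor.** The article says at least 80%, so 48 is the fewest patients it expects, not a forecast. This stands. With about 5% loss or less there is no shortfall. The defensible statement is that 0.95 does not hold over the range the plan accepts; at 90% retention it is already slightly missed.

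**Power of 0.91 is still good.** This also stands. A reader might infer that the trial is badly underpowered. The documents do not support that: on the inputs that reproduce 58, the loss at the floor is about 4 points from a demanding target.

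**The power figures rest on inferred inputs.** This is correct. The article names neither the effect tested nor the correlation. The headcount of 48 against 58 depends on neither; the power figures depend on both. On G*Power's default metric, the Group × Time test at f = 0.40 and ρ = 0.5 needs only 18 patients, so 48 would be ample. That variant does not yield 58, however, so it cannot be the calculation that the article reports.

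**Group × Time power could be much lower.** A reader might infer this by assuming a particular pattern of group differences over the three occasions. The article gives no such pattern, and any gap found that way would mix a change of test and effect with the effect of attrition. It is not part of this point.

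**Carrying the last observation forward keeps everyone in.** That analysis is conditional and is meant to assess the effects of attrition. The main efficacy comparison uses completers, so it does not restore the numbers.

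**Cybersickness exits add further loss.** A reader might count these on top of the 20%, since they can arise only in the CBT + VR group. The article gives no rate, and they may already lie within the 20%, so nothing can be added for them.

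**Conclusion.** The point holds as a moderate inconsistency in a stated design figure. A target of about 60 is consistent with the power analysis only if almost no one is lost. At the lowest retention the plan accepts, 48 patients are analysed, 10 short of 58. This follows from the article's own numbers.

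The cost in power is about 4 points at that floor (0.91 against the stated 0.95) and about 1 point at 90% retention. Both figures assume a between-groups test with f = 0.40, three occasions, 1:1 allocation and ρ = 0.5. An exact match to 58 makes these inputs plausible but does not confirm them. What needs correcting is the power claim; the number to be recruited can stay.

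**What to change.** 1. The sponsor confirms the G*Power inputs behind 58: the effect tested (between-groups or Group × Time), the effect-size metric and the correlation among repeated measures.
2. Keep about 60 recruits and replace the sentence in Recruitment that calls this number consistent with the power analysis. If the inputs are those that reproduce 58, suitable wording is: with 60 randomised and at least 80% retained (48 or more analysed), power is at least 0.91 for the assumed effect, taking a correlation of 0.5 between occasions. If the inputs differ, use the same sentence with the recalculated power at 48.

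The cost is one sentence and a slightly less favourable stated power. No extra patients and no design change are needed. Keeping 58 analysed at 80% retention would instead require 58 / 0.80 = 72.5, so 73 recruits (74 for equal groups). The size of the shortfall does not oblige the sponsor to do that.

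### The 0.95 power at n = 58 matches a large effect (f = 0.40) on the between-groups term, not an average effect, and a medium post-treatment difference gets far less

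*Protocol article*

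**What the plan says.** All from the protocol article.

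- **Recruitment:** the planned size is "We will recruit a sample of about 60 patients with GD". G*Power was used "to estimate the sample size that would be necessary to achieve a statistical power of 0.95 for a mixed ANOVA", and the result was that "a sample size of *n* = 58 was necessary in order to obtain an average effect size, equal to 0.40 (α = 0.05".
- **Design:** "Two independent groups to which patients will be randomly assigned will be considered".
- **Data Analysis:** the efficacy comparison is a mixed ANOVA with "Time* as within factor (pre-test/post-test/follow-up) and *Group* as between factor", so two groups by three occasions. On attrition: "We are expecting to find a retention rate of at least 80" per cent.
- **Discussion:** the expected result is a larger gain in self-efficacy, and larger falls in craving and cognitive distortions, with CBT + VR than with CBT alone.

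The Recruitment section does not say whether 0.40 is Cohen's f, d or another measure, which ANOVA term was powered, or what correlation between occasions was entered.

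**The concern.** The effect size is called average and set at 0.40. The usual input to ANOVA power routines is Cohen's f, on which 0.10, 0.25 and 0.40 are the conventional small, medium and large values. With two equal groups d = 2f, so f = 0.40 is d = 0.80. A value of 0.40 is near average only on the d scale, where it corresponds to f = 0.20. Label, number and sample size therefore need checking against each other.

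What is at stake is how the trial's sensitivity is understood. Both arms are active, and Table 1 gives both the same first cycle of eight traditional sessions, so 0.80 SD is a demanding difference to expect. A reader who takes the sentence at face value could treat a non-significant result as strong evidence against a moderate advantage of CBT + VR.

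**Working it through.** **Inputs from the article:** α = 0.05, power 0.95, effect 0.40, n = 58, two groups, three occasions (m = 3). **Assumed:** equal allocation, correlation r = 0.5 (software default), sphericity, a common SD on all occasions.

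**Formulas (noncentral F)**
- Group: λ = f²·N·m / (1 + (m − 1)r), df = 1 and N − 2.
- Group x Time: λ = f²·N·m / (1 − r), df = 2 and 2(N − 2).

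**Step 1: reproduce 58.** Group term, f = 0.40:
- N = 56: λ = 0.16 × 56 × 3 / 2 = 13.44, power 0.9495.
- N = 58: λ = 0.16 × 58 × 3 / 2 = 13.92, power 0.956.

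The smallest even N reaching 0.95 is exactly 58.

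**Step 2: other readings at r = 0.5.** N needed for 0.95:

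| Reading of the effect | Group | Group x Time |
|---|---|---|
| f = 0.40 | **58** | 18 |
| f = 0.25 (medium) | 142 | 44 |
| f = 0.20 (0.40 read as d) | 220 | 66 |
| 0.40 read as eta squared (f = 0.816) | 16 | 6 |

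The Group term at f = 0.40 with two occasions gives 64. The alternative effect-size options for the interaction at f = 0.40 give 52 and 34. None of these is 58.

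**Step 3: routes to 58 at another correlation.** Group x Time returns 58 for f = 0.20 with r about 0.57, and for f = 0.25 with r about 0.33. The article states neither correlation.

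**Step 4: what f = 0.40 on the Group term means.** The term compares arm means averaged over all occasions, pre-test included, so 0.80 SD is that average. Randomised arms are expected to be equal at pre-test. For differences of 0, d and d, the average is 2d/3. An average of 0.80 then needs d = 0.80 × 3/2 = 1.2 SD at both later occasions.

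**Step 5: power for a post-treatment difference.** Arms equal at pre-test, differing by d at post-test and follow-up:
- Group: f = (2d/3)/2 = d/3.
- Group x Time: the occasion differences deviate from their mean by −2d/3, d/3 and d/3, so f² = (1/3)(1/4)(4/9 + 1/9 + 1/9)d² = d²/18.

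At N = 58, r = 0.5:

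| d | Group f | Group λ | Group power | G x T f | G x T λ | G x T power |
|---|---|---|---|---|---|---|
| 0.5 | 0.167 | 2.42 | 0.33 | 0.118 | 4.83 | 0.48 |
| 0.8 | 0.267 | 6.19 | 0.69 | 0.189 | 12.37 | 0.88 |

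For d = 0.5, Group x Time would need N = 188 for 0.95.

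**Step 6: dependence on r (N = 58).** For d = 0.5, Group x Time power is 0.36 at r = 0.3, 0.48 at 0.5, 0.71 at 0.7 and 0.88 at 0.8. Group power falls from 0.40 to 0.27 over r = 0.3 to 0.8. For d = 0.8, Group x Time power runs from 0.75 (r = 0.3) through 0.945 (r = 0.6) to above 0.99 (r = 0.8).

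**Step 7: retention.** With 80% of 60, that is 48 patients, at r = 0.5, power for d = 0.5 is 0.28 (Group) or 0.40 (Group x Time).

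**The case against.** The strongest reply is that the article never states metric, term or correlation, so a contradiction is being inferred from assumed settings. On one reading (0.40 as d, entered as f = 0.20 for Group x Time with r about 0.57) the word *average*, the 0.40 and the 58 all agree. This stands in part: one cannot say that 58 arises only from f = 0.40. The default settings reproduce it exactly, which makes that route the most likely one but does not prove it.

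The second reply is that the hypothesis concerns change, so Group x Time is the relevant term, and its nominal power at N = 58 and r = 0.5 is 0.99 for f = 0.25 and 0.92 for f = 0.20. The figures are right. A reader might infer from the Group routine that power for an average effect is simply 0.63 (f = 0.25). The documents do not support that, because 0.63 belongs to a term that does not carry the hypothesis and to a difference present from pre-test onward. But the 0.99 does not rescue the claim either. Under the pattern in Step 5, interaction f = 0.25 means d = 0.25 × √18 = 1.06 SD after treatment, which is not a medium arm difference.

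It is also fair to say that relabelling 0.40 as a 0.80 SD arm difference, with nothing further, would mislead in its turn: 0.80 SD after treatment has power 0.69 or 0.88 at r = 0.5, not 0.95.

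**Conclusion.** The point holds in this form. On the most likely reconstruction, n = 58 with power 0.95 belongs to a large effect, f = 0.40, on the Group main effect: 0.80 SD averaged over three occasions including pre-test. Calling that effect average misdescribes it, and the term is not the one that tests for greater change. For a medium post-treatment difference of 0.5 SD, power at 58 is about 0.33 (Group) or 0.48 (Group x Time) at r = 0.5. Neither term reaches 0.95 anywhere in r = 0.3 to 0.8.

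This rests on r = 0.5 for the reconstruction, equal allocation, sphericity, and arms equal at pre-test with the same difference at both later occasions. The Group x Time figure is sensitive to the correlation, from 0.36 to 0.88 over that range.

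A reader might go further and conclude that the trial is too small and must be enlarged. The documents do not support that: they do not establish which difference is worth detecting, and the unstated settings could alter the reconstruction. What needs correcting is the power statement, not the planned number.

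**What to change.** Keep the target of about 60. In the Recruitment section:

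1. Delete *average* and state the metric, the ANOVA term and the correlation actually entered, taken from the software output. If the reconstruction is right: Cohen's f = 0.40 (large), Group main effect, r = 0.5, equivalent to 0.80 SD averaged over pre-test, post-test and follow-up.
2. Add the power for Group x Time under a medium post-treatment difference: about 0.48 at N = 58 and r = 0.5 for 0.5 SD at post-test and follow-up, with a range over plausible correlations (0.36 to 0.88 for r = 0.3 to 0.8).
3. If the output shows another route to 58, print that route's metric, term and correlation instead, and still give item 2.

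In Data Analysis, say that arm differences will be reported with confidence intervals, so that a non-significant result is not read as ruling out a moderate benefit.

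The cost is a few sentences and no extra patients. The downside is a visibly less favourable stated power.
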